#### 2.4.2. Phase 2: Intervention group

Patients in the intervention group will receive multidisciplinary MR. Pharmaceutical patient care will be provided by six clinical pharmacists who have extensive experience in the MR process Additionally, they have a strong understanding of geriatric pharmacotherapy and, in this study, the clinical pharmacists are responsible for the entire MR service. Along with the nursing record of preadmission medications at the time of admission, pharmacists will obtain the BPMH by patient interview and “My Medication at a Glance” service provided by Health Insurance Review & Assessment Service (HIRA) before surgery. “My Medication at a Glance” is a government-run service that provides access to patient history of prescribed medications for the last 1 year with their consent. However, it only contains information on reimbursed drugs; therefore, we will interview patients to obtain accurate lists of medications that they are actually taking, including all prescribed medications, over-the-counter medications, and dietary supplements. Drug name, dose, frequency, indication, duration of therapy, brand, and route of administration will be noted. After acquiring the BPMH, the pharmacist documents it in electronic medical record and shares it with other healthcare professionals. Additionally, health professionals will measure frailty according to the Korean-translated version of the CFS.

During hospitalization, pharmacists will review the patient’s BPMH and compare it with the physician’s orders and in-hospital medication records. If any discrepancies are found, pharmacists will investigate the reason for the discrepancy in the EMR. If the reason is not documented in the EMR, doctors are consulted to determine whether the discrepancy is intentional or unintentional. If the discrepancy is intentional, doctors are encouraged to document the reasons in the EMR. If unintentional, the discrepancy will be mediated. If DRPs are identified, pharmacists and doctors will collaborate to resolve them.

Upon discharge, pharmacists will review discharge medications and compare them with the BPMH. Any discrepancies will be addressed, and pharmacists will provide counselling regarding discharge medications and medication changes. They will also provide patient-friendly updated written medication lists that include information on newly added, changed, and discontinued medications. If a patient is discharged on the weekend, pharmacist-led counselling will be conducted via telephone on the next weekday.

At the first outpatient visit after discharge, pharmacists will meet the patients and enquire about their health and medication issues, including DRPs, ED visits, and unscheduled readmission. Additionally, patients will be asked to complete a survey that includes questions about their satisfaction with the MR service and whether their understanding of their medications has improved. Similar to the control group, the pharmacists will contact the patients by phone 30 days after discharge to obtain information about their health and medication issues, including DRPs, ED visits, and unscheduled readmissions.

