### 2.4. Intervention

#### 2.4.1. Phase 1: Control group

Patients enrolled in the control group will receive the usual standard of care. Pre-admission medications will be obtained by nurses. During hospitalization, health professionals will measure frailty according to the Korean-translated version of the Clinical Frailty Scale (CFS) [10]. Patients will receive discharge medication counseling as a part of discharge summary from the medical team. However, pharmacists will not be involved in the discharge process. At the first outpatient visit after the discharge, which will take place around 14 days after the discharge, the patients in the control group will receive face-to-face medication counseling from pharmacists. The counseling will include an assessment of the patients’ preadmission medications, and an identification of any discrepancies and DRPs. The patients will also be asked whether they had any ED visits or unscheduled readmissions after discharge. Additionally, pharmacists will conduct a post-discharge phone call with patients 30 days after the discharge to enquire about any DRPs, ED visits, or unscheduled readmissions, and their causes. The patients will be interviewed and asked specific questions pertaining to various aspects related to their health and medication. These questions include inquiries about possible side effects, any new symptoms experienced, history of outpatient or inpatient visits following their discharge, and any changes made to their current medications.

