#### 2.5.2. Secondary Outcome

The secondary endpoints are to (1) estimate the incidence rate of medication discrepancies at each transition and the discrepancy rate among the sources of information, (2) explore the impact of MR services on the medication appropriateness index (MAI) score [12], the rate of DRPs within 14 days and 30 days after discharge, 30 day mortality, ED visit rate, and readmission rate after discharge, (3) investigate the rate and acceptability of pharmacist interventions during hospitalization, and (4) explore patient satisfaction among the intervention group.

The DRP characteristics will be described using the Pharmaceutical Care Network Europe (PCNE) DRP classification [13]. The incidence rate of medication discrepancies will be calculated by dividing the number of patients with at least one discrepancy by the total number of patients in each group.

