### 2.8. Statistical Analysis

An intention-to-treat analysis will be conducted. The baseline characteristics will be summarized with descriptive statistics. Primary and secondary endpoints, except the rate and acceptability of pharmacist interventions during hospitalization, will be compared between the control and intervention groups. Categorical variables will be analyzed using the chi-square test or Fischer’s exact test, and continuous variables will be analyzed using the Student’s *t*-test or Mann–Whitney test. Data analysis will be performed after the data for the entire sample have been collected, using SAS version 9.4 (2017 SAS Institute, Cary, NC, USA) with a significance level of 0.05 and the limits of a confidence interval of 95%.

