## 3. Discussion

The MERITS trial aims to evaluate the effect of a multidisciplinary MR service on medication management and patient outcomes during transitional care in older patients undergoing thoracic and cardiovascular surgeries. To the best of our knowledge, the MERITS trial is the first prospective study to evaluate the impact of implementing MR services in the Republic of Korea.

This study protocol is prone to several limitations. First, it will be conducted at a single center and target a specific population, which may limit its generalizability to other settings. Second, the MR service will be implemented only during weekdays, which may result in negative outcomes because MR may be more necessary on weekends owing to limited staff and shifts. Third, due to the before–after study design, the study cannot be blinded, which increases the risk of bias. Therefore, this study will use strategies to reduce observer bias, such as providing minimal information to the medical staff in the control group.

Although these limitations are important, the results of this study may contribute to the development of multidisciplinary MR services in cardiothoracic wards and improve patient safety during care transitions.

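### At the first outpatient visit the described way of finding drug-related problems (DRPs) differs between the groups, so the compared DRP rate may partly reflect how DRPs were looked for

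*Protocol article*

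**What the plan says.** Protocol article, 2.5.2 (Secondary Outcome) lists "the rate of DRPs within 14 days and 30 days after discharge" among the secondary endpoints. Section 2.8 says that primary and secondary endpoints, apart from those on pharmacist interventions, "will be compared between the control and intervention groups". Table 1 schedules DRPs at the first outpatient visit and at 30 days, without separating the groups.

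For the first outpatient visit, 2.4.1 gives controls a face-to-face session with a pharmacist. It covers an assessment of "preadmission medications, and an identification of any discrepancies and DRPs". For the same visit in the intervention group, 2.4.2 says that "pharmacists will meet the patients and enquire about their health and medication issues, including DRPs, ED visits, and unscheduled readmission", and adds a satisfaction survey.

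For day 30, 2.4.1 has pharmacists telephone controls "30 days after the discharge to enquire about any DRPs, ED visits, or unscheduled readmissions, and their causes". Section 2.4.2 states equivalence for this contact: "Similar to the control group, the pharmacists will contact the patients by phone 30 days after discharge".

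**The concern.** A rate can be compared between groups only if its events are looked for in the same way in both. Here the text gives a medication assessment with DRP identification on one side and an enquiry on the other, at the same visit and for the same endpoint. A review of a drug list can uncover problems that a patient would not volunteer, such as a duplicated drug, a drug without an indication or a wrong dose. If the two visits really differ in this way, controls may have more DRPs recorded for the same underlying problems, and the service would appear to reduce DRPs without having done so.

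The 14-day rate is affected directly. The 30-day rate is affected if it is cumulative, because findings from the visit then carry forward. This concerns how the endpoint is counted, and is separate from whether the control visit itself acts as a treatment.

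**Working it through.** **1. The contacts side by side**

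| Contact | Control (2.4.1) | Intervention (2.4.2) | Stated to be alike? |
|---|---|---|---|
| First outpatient visit, about day 14 | Pharmacist assesses preadmission medications; discrepancies and DRPs identified | Pharmacist meets the patient and enquires, DRPs included; survey | No |
| 30-day call | Pharmacist enquires by phone | Pharmacist enquires by phone | Yes |

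Section 2.4.1 uses both kinds of wording: assessment and identification for the visit, enquiry for the call. Section 2.4.2 uses the language of enquiry for the visit. That makes the contrast more than a stray verb, though it does not prove that practice differs.

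**2. The plan's own figure**

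The sample size in 2.6 concerns the primary outcome (discrepancies), not DRPs. It supplies the group sizes used below. Inputs from 2.6: 40% in controls, a 40% relative reduction (so 24%), alpha 5% (taken as two-sided), power 80%, 10% loss, two intervention patients per control.

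n(control) = [1.96·√(p̄(1−p̄)·1.5) + 0.842·√(p₁(1−p₁) + p₂(1−p₂)/2)]² / (p₁−p₂)²

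With p₁ = 0.40, p₂ = 0.24 and p̄ = (0.40 + 2×0.24)/3 = 0.293, this gives 98 controls and 196 intervention patients. Multiplying by 1.10 gives 107.8 and 215.6, that is 108 and 216, as stated. The sample size reproduces and is not in question.

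**3. How far unequal ascertainment could move the DRP comparison**

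The documents give no expected DRP rate for this trial and no yield for either procedure, so this step is an illustration.

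- Analysed: 108 × 0.9 ≈ 97 controls and 216 × 0.9 ≈ 194 intervention patients.
- The true proportion p with at least one DRP is the same in both groups. Two values are tried: 40% (borrowed from the discrepancy rate in 2.6) and 63.7% (a cited study's post-discharge DRP figure, section 1).
- Controls record p. The intervention group records q = r·p, where r is the assumed relative yield.
- Two-proportion z-test, two-sided 5%. With p̄ = (97p + 194q)/291, SE₀ = √[p̄(1−p̄)(1/97 + 1/194)] and SE₁ = √[p(1−p)/97 + q(1−q)/194], the chance of a false significant reduction is Φ[((p − q) − 1.96·SE₀)/SE₁].

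Worked case, p = 0.40 and r = 0.9: q = 0.36, p̄ = 0.373, SE₀ = 0.0601, SE₁ = 0.0605. Then (0.040 − 0.118)/0.0605 = −1.29, and Φ = 0.099.

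| Relative yield r | Chance of a false reduction, p = 40% | p = 63.7% |
|---|---|---|
| 1.00 | 2.5% | 2.5% |
| 0.95 | 5% | 7.5% |
| 0.90 | 10% | 18% |
| 0.85 | 17% | 34% |
| 0.80 | 27% | 54% |

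The false differences behind the last column are 3.2, 6.4, 9.6 and 12.7 points, from 0.637 × (1 − r).

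**4. The other direction**

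If the intervention visit finds more, say r = 1.10 at p = 0.40, then q = 0.44, SE₀ = 0.0615 and SE₁ = 0.0612. The chance of a false reduction drops to Φ[(−0.040 − 0.1205)/0.0612] = Φ(−2.62) = 0.4%. The chance of a false increase becomes Φ[(0.040 − 0.1205)/0.0612] = Φ(−1.32) = 9%. The rates are still not comparable, and a real benefit could be masked.

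**The case against.** The strongest defence is that this is a condensed article and much is being read into wording. Pharmacists conduct the visit in both groups, and nothing in 2.4.2 says that the drug list goes unreviewed there. Table 1 has one DRP schedule, and 2.5.2 names one DRP classification (PCNE). The control assessment may simply make up for a review that controls had not had: 2.4.1 has nurses record their preadmission medications and keeps pharmacists out of discharge. Intervention patients are reviewed by pharmacists at admission, during the stay and at discharge.

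Much of this stands, and it rules out several stronger readings that a reader might infer:

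- *That intervention DRPs are found only by asking the patient.* The text does not say so. It supports only that the described procedures differ.
- *That controls get a full review of current medications.* Section 2.4.1 names preadmission medications.
- *That the bias must favour the service.* Intervention pharmacists already hold the best possible medication history and the reviewed discharge list, which could raise detection.
- *That all post-discharge DRP ascertainment differs.* The 30-day call is described as similar.
- *That the 30-day rate is cumulative and a chi-square test will be used.* Both are plausible, but 2.5.2 gives no counting rule for DRPs, and 2.8 offers several tests by type of variable.

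The defence does not remove the core. The earlier inpatient reviews precede the post-discharge window and do not show that DRPs are sought alike within it. The article does not merely leave the visit undescribed: it describes it for both groups, differently, and claims similarity only for the other contact. The Discussion also concedes that "the study cannot be blinded, which increases the risk of bias", so nothing in the article shields DRP counting from knowledge of group.

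**Conclusion.** The point holds in a limited form. At about day 14 the article describes different DRP ascertainment in the two groups, for a secondary endpoint that is compared between them. The 14-day rate is exposed, and the 30-day rate too if it is cumulative. A bias towards the service is likelier than the reverse, but it is not established.

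The size depends on assumptions. With equal true rates and 97 versus 194 analysed, relative yields of 90% and 80% give a chance of a false significant reduction of about 10% and 27% at a true rate of 40%, and 18% and 54% at 63.7%, against a nominal 2.5%. These figures show that a modest difference in yield would matter; they do not show that one exists. The primary outcome and the sample size are untouched. The change should be made, but the main conclusion of the trial does not depend on it.

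**What to change.** Reconcile 2.4.1 and 2.4.2 so that one DRP procedure applies to both groups at the first outpatient visit: the same medication review, the same question set and the same PCNE coding, recorded before any advice or the satisfaction survey. State in 2.5.2 that only DRPs found by this procedure at the visit count in the between-group comparison, and whether the 30-day rate is cumulative. If the full protocol already uses one procedure, a one-line correction of the article is enough.

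Section 2.10 says that phase 2 is under way. If patients have already been seen under a different procedure, report the 14-day comparison, and any cumulative 30-day rate, as descriptive. Show the findings of the 30-day call separately. That call is not a clean substitute, because counselling of controls at day 14 may have changed what remained to be found by day 30, and the report should say so.

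The cost is a short amendment and a slightly longer phase 2 visit, at which pharmacists already meet the patients. The observed DRP reduction may be smaller, patients already seen cannot be re-assessed, and a change partway through phase 2 leaves two procedures within that group, which is why the earlier patients need separate handling.

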### 2.5. Outcomes Measurement

#### 2.5.1. Primary Outcome

The primary outcome is to evaluate the impact of MR on medication discrepancies between BPMH and medications at care transition in the intervention and control groups. In general, medication discrepancies are classified into three categories: intentional, undocumented intentional, and unintentional discrepancies. In this study, medication discrepancies are defined as unintentional discrepancies and undocumented intentional discrepancies. Medication discrepancies will be further classified into subcategories including medication omission; incorrect dose, route, or frequency; incomplete prescription; commission without indication; therapeutic duplication; and wrong medication [11].

#### 2.5.2. Secondary Outcome

The secondary endpoints are to (1) estimate the incidence rate of medication discrepancies at each transition and the discrepancy rate among the sources of information, (2) explore the impact of MR services on the medication appropriateness index (MAI) score [12], the rate of DRPs within 14 days and 30 days after discharge, 30 day mortality, ED visit rate, and readmission rate after discharge, (3) investigate the rate and acceptability of pharmacist interventions during hospitalization, and (4) explore patient satisfaction among the intervention group.

The DRP characteristics will be described using the Pharmaceutical Care Network Europe (PCNE) DRP classification [13]. The incidence rate of medication discrepancies will be calculated by dividing the number of patients with at least one discrepancy by the total number of patients in each group.

### 2.6. Sample Size

The sample size calculation is based on the previous literature that referred to the incidence of medication discrepancies. The percentage of patients with at least one medication discrepancy varied based on ranged from 14.1% to 81.9% based on population and illness [14,15,16,17]. In a prospective French study, after proactive MR, the proportion of patients with at least one medication discrepancy decreased significantly from 45.8% to 2.07% (*p* < 0.001) [18]. Another study assessed MR in patients scheduled to undergo surgery, and the medication discrepancy rate in the intervention group decreased from 40.2% to 12.9% compared to that in the non-intervention group [19]. Using the reference rate of medication discrepancies reported in a previous study, it was estimated that 40% of the patients could experience at least one medication discrepancy, and the intervention may reduce these discrepancies by 40%. Assuming an alpha error of 5%, statistical power of 80%, and a 10% patient loss, the calculated sample size was 216 for the intervention group and 108 for the control group.

### 2.7. Data Collection and Management

Data will be collected from all enrolled patients, including demographic information, such as age, sex, body mass index, height, and weight. Information regarding comorbidities, pre-and postoperative diagnoses, type of surgery, and any postoperative complications will also be collected. Additionally, medication lists at preadmission, admission, and discharge; length of hospital stay; and any readmission or ED visits and their reason within 30 days after the discharge will be documented. Table 1 presents the outcome variables for the evaluation period and the measuring instruments used.

### 2.8. Statistical Analysis

An intention-to-treat analysis will be conducted. The baseline characteristics will be summarized with descriptive statistics. Primary and secondary endpoints, except the rate and acceptability of pharmacist interventions during hospitalization, will be compared between the control and intervention groups. Categorical variables will be analyzed using the chi-square test or Fischer’s exact test, and continuous variables will be analyzed using the Student’s *t*-test or Mann–Whitney test. Data analysis will be performed after the data for the entire sample have been collected, using SAS version 9.4 (2017 SAS Institute, Cary, NC, USA) with a significance level of 0.05 and the limits of a confidence interval of 95%.

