## 2. Materials and Methods

### 2.1. Design

This study was reviewed and approved by the Institutional Review Board of Seoul National University Hospital (IRB No 2109-135-1257). This is a single-center, prospective, controlled, before-and-after study comparing two patient care strategies: (1) the control group, receiving standard care; (2) the intervention group, receiving multidisciplinary MR service. Depending on the time period of each patient’s participation, they will be assigned to either the control group or the intervention group. The study will initially enroll patients into the control group. Once the enrollment for the control group is completed, the study will proceed to enroll patients into the intervention group. Study enrolment started in December 2021, and the study is expected to be completed within 3 years. There are two phases in this study. Phase 1 (control group) will last about four months, and phase 2 (intervention group) will last eight months.

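### A comparison of two consecutive calendar periods is to be tested only with unadjusted tests, so measured case-mix differences between phases would be read as an effect of the service

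*Protocol article*

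**What the plan says.** Section 2.1 (Design) of the protocol article describes a "single-center, prospective, controlled, before-and-after study" and sets out how the groups arise: "Depending on the time period of each patient’s participation, they will be assigned to either the control group or the intervention group". The phases do not overlap: "Once the enrollment for the control group is completed, the study will proceed to enroll patients into the intervention group". They also differ in length: "Phase 1 (control group) will last about four months, and phase 2 (intervention group) will last eight months". Section 2.2 places the whole study in the same five wards of one hospital. No group without the service is described during phase 2.

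Section 2.8 (Statistical Analysis) says that the primary and secondary endpoints, apart from pharmacist interventions, are compared between the groups. For proportions the method named is: "Categorical variables will be analyzed using the chi-square test", with Fisher's exact test as the alternative. For measurements on a scale it is a two-sample test of the same crude kind: "continuous variables will be analyzed using the Student’s *t*-test or Mann–Whitney test". Baseline characteristics are to be described. No regression, weighting, matching, stratification or time term is mentioned.

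Section 2.7 lists age, sex and the medication lists among the data collected, and adds: "Information regarding comorbidities, pre-and postoperative diagnoses, type of surgery, and any postoperative complications will also be collected". The Discussion ties the before-after design to lack of blinding and observer bias. It does not mention case mix or secular change.

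**The concern.** A chi-square or t-test reads any difference between the groups as either chance or the intervention. Randomisation justifies that reading; assignment by calendar period does not. The stated 0.05 level then holds only if the two periods would have had the same discrepancy risk without the service. Section 2.6 itself cites discrepancy percentages from 14.1% to 81.9% across populations and illnesses, so the authors accept that the outcome varies with the type of patient. A phase of about four months and one of eight cover different parts of the year, and nothing in the design keeps the surgical mix the same.

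The primary conclusion is at stake. A milder case mix in phase 2 would imitate a benefit, and a heavier one would hide a real benefit. The variables that could remove the measured part of this are mostly in the database, but the named analysis does not use them.

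**Working it through.** **1. Inputs.** From section 2.6: 40% of control patients with at least one discrepancy; a 40% relative reduction, so 0.40 × (1 − 0.40) = 24% under the service; alpha 5%; power 80%; 10% loss; 108 control and 216 intervention patients. Sidedness is not stated; two-sided is assumed because it reproduces the figure. The patient-level proportion is taken as the primary measure because the sample size rests on it.

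**2. The plan's own figure.** For a pooled two-proportion test with ratio k = 2:

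n(control) = [1.960·√(p̄(1−p̄)(1+1/k)) + 0.8416·√(p1(1−p1)+p2(1−p2)/k)]² / (p1−p2)²

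Here p̄ = (0.40 + 2×0.24)/3 = 0.2933, so n = (1.0929 + 0.4844)² / 0.16² = 97.2. That gives 98 control and 196 intervention patients. Multiplying by 1.10 gives 107.8 and 215.6, that is 108 and 216, as stated. Dividing by 0.90 would give 109 and 218. The design was therefore sized for an unadjusted comparison of two proportions, in line with section 2.8.

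**3. Rejection probability with no service effect.** After 10% loss: 108 × 0.9 ≈ 97 and 216 × 0.9 ≈ 194. Let the underlying risk be 0.40 in phase 1 and 0.40 − d in phase 2, with p̄ the pooled rate over all 291 patients.

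- SE0 = √(p̄(1−p̄)(1/97+1/194))
- SE1 = √(p1(1−p1)/97 + p2(1−p2)/194)
- P(reject) = Φ((d − 1.960·SE0)/SE1) + Φ((−d − 1.960·SE0)/SE1)

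For d = 0.05: p̄ = 0.3667, SE0 = 0.0599, SE1 = 0.0604, and P = Φ(−1.117) + Φ(−2.773) = 0.132 + 0.003 = 0.135.

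| Assumed drop d | P(reject), nominal 5% |
|---|---|
| 0 | 5.0% |
| 3 points | 8.0% |
| 5 points | 13.5% |
| 8 points | 27.5% |
| 10 points | 40.2% |

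**4. A single case-mix factor.** Take a binary factor present in 50% of phase 1 patients, with the overall phase 1 risk held at 40%. If its prevalence falls to 40%, 35% or 30% in phase 2, the rejection probability is 5.9%, 7.0% or 8.6% when its odds ratio is 2, and 7.2%, 9.9% or 13.9% when it is 3. Both the prevalences and the odds ratios are assumptions.

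**5. The other direction.** Suppose the underlying risk rises from 40% to 45% and the service still cuts it by 40%. The phase 2 rate is then 0.45 × 0.60 = 27%. The first term of the formula in step 3, with p1 = 0.40 and p2 = 0.27 (SE0 = 0.0577, SE1 = 0.0591), is Φ(0.287) = 61%. At the planned 24% it is 79.9%.

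**6. Room for a model.** Expected patients with a discrepancy: 97 × 0.40 + 194 × 0.24 = 38.8 + 46.6 ≈ 85. That supports a small covariate set, not a long one.

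**7. Can monthly rates reveal a trend?** About 97/4 ≈ 24 control patients per month gives a standard error of √(0.40×0.60/24) ≈ 0.10, so 95% limits of about ±20 points. A drift of 3 to 10 points would not show.

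**The case against.** The strongest reply is that section 2.8 is a short paragraph in a condensed article. It lists default tests by type of variable and does not exclude adjustment, and a statistical analysis plan that is not shown could add a model. That stands as a caution: a reader might infer that the trial has ruled out adjustment, and the article does not say so. But the article does name the between-group tests, all of them crude, and the sample size matches a crude test. The point rests on that stated choice, not on missing detail.

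A second reply is that the size is assumed. This stands in full. No figure in the documents supports a shift of 3 to 10 points, and the single-factor scenarios give smaller inflation. A reader might infer that the result will be falsely positive; the documents support neither that size nor that direction.

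A third reply concerns the remedy, and it narrows it.
- A reader might infer that every useful covariate is already available in comparable form. Sections 2.4.1 and 2.4.2 say otherwise for the preadmission drug list. Nurses record it in both phases, but the pharmacist history taken before surgery from interview and the national prescription record is described only for phase 2. A drug count from the fuller source would differ by phase through measurement alone.
- Table 1 places the frailty score under hospitalization, so it is not documented as a preoperative value. With phase 2 under way (section 2.10), control-phase scoring can no longer be changed.
- A reader might infer that adjustment removes calendar effects. It does not, because phase and calendar time coincide, and step 7 shows that monthly rates would not expose a trend of the assumed size.

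Finally, the word controlled in the design label might be called misleading. Section 2.1 states the sequence openly, and relabelling would change no result, so it is not part of this point.

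**Conclusion.** The concern holds for the choice of test. Groups formed by consecutive periods are to be compared with unadjusted tests, so a measured case-mix difference would count as an effect of the service. With 97 and 194 patients, a control risk of 40% and no true effect, assumed drops of 3 to 10 points in underlying risk raise the nominal 5% error to between 8% and 40%. One moderately imbalanced factor gives about 6% to 14%. The real shift is unknown and could act in either direction. The sample size is not at fault. Inability to separate a secular trend from the service is a limit of the design that no analysis of these two periods removes; it has to be stated.

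**What to change.** Before the data are analysed, make a covariate-adjusted comparison of patients with at least one discrepancy the primary analysis. Modified Poisson regression, or logistic regression with standardisation to a risk difference and ratio, would serve.

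- Prespecify a small set of preoperative covariates measured the same way in both phases: age, sex, comorbidity, and type of surgery in few categories, kept within the roughly 85 expected events.
- Add the number of preadmission drugs only from the source common to both phases, the nursing record.
- Add frailty only if it is confirmed that the score reflects preoperative status in both phases.
- Do not adjust for postoperative complications, which arise after the service has begun.
- Keep the chi-square test as supportive.
- State as a limitation that adjustment covers measured case mix only, so a secular trend cannot be separated from the service effect.

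Section 2.8 defers analysis until the whole sample is collected, so this can still be settled beforehand. The cost is some wording, a little more analysis work and reliance on a model. The core covariates need no new data collection.
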